**Figure 4 F4:**
[figure not shown]
**Stylets used in the intervention arms. (a)** Conventional Portex™ intubation stylet used in group A patients. **(b)** Truflex™ articulating stylet with stopper used in group B patients.

Primary efficacy endpoints will be successful or failed tracheal intubation in the first attempt, total intubation time and the intubation difficulty score. An attempt will be counted if the laryngoscope or the ETT needs to be removed for re-oxygenation (drop in oxygen saturation by 5%) or for reshaping of the ETT. The total intubation time will be the sum of the glotticoscopy time (from introduction of the videolaryngoscope blade between the teeth to the best laryngeal view) and the ETT negotiation time (from receiving the styleted ETT in laryngoscopist’s hand to passage of the black line just beyond the vocal cord). Secondary efficacy endpoints will be overall user satisfaction graded from 1 to 10 (1 = very poor, 10 = excellent), Cormack and Lehane’s grading, glotticoscopy time and ETT negotiation time and total number of intubation attempts with a maximum of three attempts, after which an alternative technique will be used. Safety endpoints assessed will be dental and airway trauma (present or absent), hemodynamic disturbances (blood pressure and pulse rate would be recorded before intubation, 1 minute and 5 minutes post-intubation; ≥20% change from the baseline value will be considered clinically important), arrhythmias (absent or present; type if present), or cardiac arrest.

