**Methods:**

One hundred and fifty four patients between 18 and 60 years of age belonging to either sex undergoing tracheal intubation under uniform general anesthetic technique will be randomly divided into Portex™ malleable stylet group and Truflex™ articulating stylet group. The primary efficacy variable of success/failure between the two groups will be analyzed using the chi square test. For comparison of intubation times and the Intubation Difficulty Score, ANOVA will be used. Primary efficacy endpoint results will be successful or failed tracheal intubation in the first attempt, total intubation time and the intubation difficulty score. Secondary efficacy endpoints will be overall user satisfaction graded from 1 to 10 (1 = very poor, 10 = excellent), Cormack and Lehane’s grading, glotticoscopy time and ETT negotiation time and total number of intubation attempts. Result of safety endpoints will include dental and airway trauma, hemodynamic disturbances, arrhythmias or cardiac arrest.

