The present trial (ISRCTN57679531) aims at utilizing the Truflex™ articulating stylet (TAS) (Truphatek) as a dynamic aid to tailor the ETT shape in its very first attempt as per the videolaryngoscope blade design (Figure 2) and the patient’s oropharyngeal anatomy. We hypothesize that a pre-loaded ETT over the TAS will not only shorten the D-blade C-Mac™ videolaryngoscope-aided intubation time, but will also attenuate the hemodynamic response and reduce the possibility of soft-tissue trauma, both in patients with normal anatomy and in those whose anatomy makes access more difficult, compared to non-dynamic PIS-aided tracheal intubation.

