### Statistical considerations

For sample size assessment, a pilot study of 60 patients was conducted in which we observed that successful intubation could be achieved in the first attempt in 100% (30/30) of patients in group B (TAS) but was achieved in 90% (27/30) of group A (PIS). To detect a similar difference between the success of intubation (100 versus 90%) with a statistical power of 80% and 95% confidence interval and equal distribution of patients in both the groups, a total sample size of 154 was estimated for the present study using the open source browser-based calculator OpenEpi [16]. However, in light of the stratification used for randomization the final sample size of 158 shall be used with equal distribution. All statistical evaluations will be made at a significance level of 0.05 (two-sided). A two-sided, 95% confidence interval will be calculated for the mean difference between the treatment groups. The data will be analyzed on an intention-to-treat basis. No imputations will be used for any missing data. The primary efficacy variable of success/failure between the two groups will be analyzed using the chi square/Fisher’s exact test, whichever will be applicable. Binary logistic regression will also be used on the whole dataset to identify predictors of success/failure of intubation. For evaluation of intubation times and the intubation difficulty score, analysis of variance (ANOVA) will be used for comparison between both treatment groups. The intubation difficulty scale (IDS) will also be transformed into an ordinal variable (0, 0 to 5, >5) and multinomial logistic regression will be used to evaluate for possible predictors of a difficult intubation.

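### The primary endpoint is stated inconsistently (three unranked endpoints in one place, one in another), with no rule for what makes the trial positive

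*Protocol article*

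**What the plan says.** **Three primaries.** The endpoints paragraph of Methods states: "Primary efficacy endpoints will be successful or failed tracheal intubation in the first attempt, total intubation time and the intubation difficulty score". The abstract repeats the list: "Primary efficacy endpoint results will be successful or failed tracheal intubation in the first attempt, total intubation time and the intubation difficulty score". Neither ranks them.

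**One primary.** Statistical considerations speaks in the singular: "The primary efficacy variable of success/failure between the two groups will be analyzed", by chi square or Fisher's exact test. The abstract has the same singular phrase, so it holds both versions within one paragraph. The sample size rests on this endpoint only: 100% against 90% first-attempt success, 80% power, 154 patients, raised to 158 for the stratification.

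**The other two.** They receive their own between-group test: "For evaluation of intubation times and the intubation difficulty score, analysis of variance (ANOVA) will be used for comparison between both treatment groups".

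**Error rate.** "All statistical evaluations will be made at a significance level of 0.05 (two-sided"). No order of testing, adjustment or combination rule is given.

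**Hypothesis.** The last paragraph of Background predicts that the articulating stylet will shorten intubation time, and that it "will also attenuate the hemodynamic response and reduce the possibility of soft-tissue trauma". Methods lists the latter two as safety endpoints. The hypothesis sentence does not mention first-attempt success, although the sentence before it describes shaping the tube on the first attempt.

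**The concern.** A reader of the final report could not check from this article which result was meant to decide the trial. Success, time and difficulty score could each be presented as primary, and each choice could be supported from the published text. If the choice is made after the results are known, and any one significant endpoint is taken as success, the 5% error rate no longer describes the primary conclusion.

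**Working it through.** **Inputs.** Three primary endpoints (abstract; Methods). Alpha 0.05 two-sided for each, success 100% against 90%, power 80%, 1:1 allocation, N = 154 then 158 (Statistical considerations). The document gives no correlations between endpoints, so those below are assumed.

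**1. The plan's own sample size.**
- Kelsey form: n per arm = (1.960 + 0.842)² × 2 × 0.95 × 0.05 / 0.10² = 74.6, so 75 per arm and 150 in total, within 3% of 154.
- Fleiss without continuity correction gives 148; with correction, 186.
- Exact power of Fisher's test at 77 per arm is 79.4%.

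The stated 154 is therefore close to what success alone requires, though no form tried gives it exactly. The trial is sized on success alone.

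**2. False-positive risk if any one endpoint suffices.**
- Independent tests: 1 − 0.95³ = 0.1426, or 14.3%. The Bonferroni upper bound is 3 × 0.05 = 15%.
- Equal pairwise correlation, simulated with trivariate normal statistics:

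| Assumed correlation | At least one false positive |
|---|---|
| 0 | 14.3% |
| 0.3 | 13.6% |
| 0.5 | 12.5% |
| 0.7 | 10.9% |
| 0.9 | 8.3% |

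- With Fisher's exact test for success, 79 per arm and an assumed 5–10% failure rate in both arms, the actual size of that test is 1.6–2.8%. Independence then gives 1 − 0.984 × 0.95² = 11.2% to 1 − 0.972 × 0.95² = 12.3%. Fisher's test combined with correlation was not calculated. It would be lower again, but not below 5%, because each ANOVA alone carries 5%.
- Counting only false claims in favour of one given device, independence gives 1 − 0.975³ = 7.3% against a nominal 2.5%.

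**3. If success is the sole primary.** Alpha stays at 0.05. Power at 79 per arm is 82.9% (normal approximation) or 81.4% (exact, Fisher). Fisher is probably the applicable test: 79 × 0.10 = 7.9 expected failures overall is about 4 per arm, below the usual threshold of five.

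**4. If all three are required.** There is no inflation. Joint power cannot exceed the power for success. To keep it at 80%, time and difficulty score would both have to be significant in at least 0.80/0.814 = 98% (Fisher) or 0.80/0.829 = 97% (normal approximation) of the trials in which success is significant. Nothing in the document supports that, so in practice power falls below plan.

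**5. If all three stay primary with Bonferroni.** Alpha per test is 0.05/3 = 0.0167. Success then needs 198 (Fleiss) or 200 (Kelsey) patients. At 158 its power is 69.3% (normal approximation) or 68.7% (exact, Fisher).

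**The case against.** **No any-one rule is written down.** A reader might infer that the plan, followed as written, makes any single significant endpoint a positive trial and so carries a 14% false-positive risk outright. The document does not support that. It is silent on the rule, and the inflation exists only under one of the readings it allows. This objection stands.

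**The text leans towards success.** The singular phrase appears in both the abstract and the statistics section, and the sample size rests on that endpoint. On that reading the error rate is 5%. This also stands, and it is why the fix follows that reading. It does not remove the contradiction, because the abstract and Methods are then wrong to call time and difficulty score primary.

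**14.3% is a ceiling.** It needs independent tests of exact 5% size. A failed first attempt tends to raise both time and difficulty score, so positive correlation is likely. This stands, hence the range.

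**A testing hierarchy can be left to an analysis plan.** True of the hierarchy alone. The number and identity of the primary endpoints, however, are stated here in two incompatible ways. A later plan could choose one, but would still contradict part of this text.

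**Sizing on one endpoint is ordinary.** A reader might infer that time and difficulty score are underpowered. The document does not show that: at 79 per arm a comparison of means has 80% power for about (1.960 + 0.842) × √(2/79) = 0.45 SD. No such claim is made here.

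**Conclusion.** The inconsistency in the primary endpoint is certain; it rests on the article's own statements. Its effect on the error rate is conditional. If any one endpoint is allowed to decide, the chance of a false-positive primary result is about 8–14% over assumed correlations from 0.9 down to 0, and somewhat less with Fisher's exact test. If success is the sole primary, or if all three are required, there is no inflation. An unconditional 14% would overstate the case. Each reading still leaves something to correct: sole primary contradicts the endpoint lists, all-required undermines the planned power, and any-one breaks the 5% level. The point should be settled because it determines what counts as a positive trial.

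**What to change.** In the abstract, the endpoints paragraph and the statistics section, name first-attempt success as the sole primary endpoint, since the sample size is built on it. Make total intubation time and the intubation difficulty score key secondary endpoints. Test them at two-sided 0.05 in a pre-stated order, each only if the preceding test is significant. Time and then difficulty score is one possible order; the text does not dictate it. Reword the hypothesis in Background so that it includes first-attempt success and shows which of its other elements are secondary or safety outcomes.

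**Cost.** Wording only, with no added patients. The real price is that confirmatory claims on time and difficulty score depend on the primary. Even at the planned effect there is a chance of roughly 17–19% (1 − 0.829 to 1 − 0.814) that success is not significant, and intubation time, which leads the hypothesis, then cannot be claimed. If that is unacceptable, splitting alpha equally across the three is the alternative, at about 198–200 patients. The article reports 11 patients recruited at submission and says nothing of later enrolment; the choice should be fixed and dated before any comparative results are seen.

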## Abstract

**Background:**

A variety of videolaryngoscopes with angulated blade have been recently introduced into clinical practice. They provide an indirect view of the glottic structures in normal and challenging clinical settings. Despite the very good visualization of the laryngeal structures by these devices, the insertion and advancement of the endotracheal tube may be prolonged and occasionally fail as it does not conform to the enhanced angulation of the blade. To overcome this handicap, it is recommended to use a pre-shaped, styleted tracheal tube during intubation. Unfortunately, these malleable rigid stylets permit only a fixed shape to the advancing endotracheal tube. This may necessitate withdrawal of endotracheal tube-stylet assembly for reshaping, before undertaking a new attempt. This may cause soft tissue injury and hemodynamic disturbance.

This single-blinded randomized clinical trial aims to overcome these handicaps using a novel method of dynamically changing the shape of the advancing endotracheal tube by Truflex™ articulating stylet as per need during D-blade C-Mac™ videolaryngoscopy.

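### Total intubation time, a listed primary endpoint, has no workable clock for patients who need more than one attempt and no value for patients never intubated with the stylet

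*Protocol article*

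**What the plan says.** The Methods section (endpoint paragraph after Figure 4) lists as primary efficacy endpoints "successful or failed tracheal intubation in the first attempt, total intubation time and the intubation difficulty score". It then defines the time endpoint: "The total intubation time will be the sum of the glotticoscopy time" and the negotiation time. The two parts are:

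- Glotticoscopy time: "from introduction of the videolaryngoscope blade between the teeth to the best laryngeal view".
- Negotiation time: it starts when the operator is handed the tube on its stylet and runs "to passage of the black line just beyond the vocal cord".

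The same paragraph plans for repeat attempts. "An attempt will be counted if the laryngoscope or the ETT needs to be removed for re-oxygenation", or for reshaping of the tube. The secondary endpoints include "total number of intubation attempts with a maximum of three attempts, after which an alternative technique will be used".

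Under Statistical considerations, the times are compared by ANOVA, the analysis is by intention to treat, and "No imputations will be used for any missing data".

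On the fixed shape of rigid stylets, the Abstract (Background) says: "This may necessitate withdrawal of endotracheal tube-stylet assembly for reshaping, before undertaking a new attempt". The Background section adds that removal and reshaping may delay intubation, and hypothesizes that the articulating stylet (TAS) shortens intubation time compared with the Portex stylet (PIS).

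**The concern.** The definition fits a patient intubated on the first pass. It does not fit a patient whose tube or blade is taken out, because a removed attempt has no cord passage and so no closed negotiation interval. Nothing says whether the clocks then restart, add up over attempts, or run on from the first handover of the tube. Two observers could time the same patient differently and both comply.

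The ambiguity falls on the patients who matter most to the hypothesis. The delay that the articulating stylet is meant to remove arises in repeat attempts, and the pilot saw those only with PIS. A rule that leaves the delay out pulls the comparison toward no difference, while one that counts some of it twice pushes the other way. A patient passed to an alternative technique has no end event, so the worst outcomes are the ones with no value to analyse.

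**Working it through.** **1. One two-attempt patient under each reading.** Let G1 and G2 be the glotticoscopy times, F the time from first handover of the tube to its removal, W the time for withdrawal, reshaping and re-oxygenation, and N the negotiation time of the successful pass. Ignoring handover gaps, and with the blade re-inserted, elapsed time is G1 + F + W + G2 + N.

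| Reading of the definition | Recorded time | Error |
|---|---|---|
| Successful attempt only | G2 + N | omits G1 + F + W |
| Closed intervals added over attempts | G1 + G2 + N | omits F + W |
| Negotiation from first handover, G1 added | G1 + (F + W + G2 + N) | none |
| As above, every glotticoscopy added | G1 + G2 + (F + W + G2 + N) | counts G2 twice |

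If the blade is removed for re-oxygenation before the tube is handed over, even the first-handover readings lose that delay, because it falls after one interval and before the other.

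**2. The plan's own figure.** The article gives a total of 154 for 100% versus 90% first-attempt success, 80% power and two-sided 0.05. With pooled variance in both terms, n per arm = (1.960 + 0.842)² × 2 × 0.95 × 0.05 / 0.10² = 74.6, so 75 per arm and 150 in total. Entering 99.9% for 100% (an assumption) gives 76.8, so 77 per arm and 154. The figure therefore reproduces closely. It concerns first-attempt success and says nothing about the time endpoint, for which the article gives no mean, SD or target difference.

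**3. Size if only the successful pass is timed.** Inputs: 158 / 2 = 79 per arm, and pilot first-attempt failures of 3/30 = 10% (PIS) and 0/30 = 0% (TAS). Expected PIS patients with a further attempt: 0.10 × 79 = 7.9. With D the mean uncounted delay (assumed), the understatement of the mean difference is (0.10 − 0) × D:

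- D = 30 s: 3 s
- D = 60 s: 6 s
- D = 90 s: 9 s

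**4. What that could do to the test.** This is an illustration on assumed inputs: 79 per arm, single-pass time of mean 30 s and SD 10 s in both arms, delay D in 10% of PIS patients only, and 4,000 simulated trials per value of D. With the delay left out, ANOVA rejects in about 5% of trials. With it included, ANOVA rejects in about 35% (D = 30 s), 67% (60 s) and 79% (90 s).

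**5. Patients with no value.** Let q be the failure rate at attempts 2 and 3 (assumed). Expected never-intubated PIS patients are 79 × 0.10 × q²:

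- q = 0.1: 0.08
- q = 0.3: 0.7
- q = 0.5: 2.0

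At the pilot rate, the expected number on TAS is about 0.

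**6. How firm the asymmetry is.** The exact 95% upper limit for 0/30 failures is 1 − 0.025^(1/30) = 0.116, or about 12%. A TAS failure rate as high as the PIS pilot rate is therefore not excluded. In that case the understatement in step 3 would shrink toward zero.

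**The case against.** The strongest reply is that the article nowhere excludes failed attempts or reshaping. Negotiation time can be read as running from first handover to final passage, which takes in most of the delay. This is right: a reader might infer a stated exclusion, and the text does not support that. The defect is an undefined clock. The alternative reading does not repair it, because it still loses a removal that precedes handover and can count a repeat glotticoscopy twice.

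Second, repeat attempts are visible elsewhere. Removal for reshaping counts as an attempt, so it bears on first-attempt success, the primary endpoint on which the sample size rests, and on the number of attempts. That also stands: the trial would not be blind to repeat attempts. But those endpoints count events and do not measure delay, and they do not make the time endpoint interpretable.

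Third, a patient without a time is a missing-data matter that a full protocol or SAP could settle, and is not analysis outside the assigned arm. This stands in part. No passage says such patients are dropped, and the expected number is small. But the article itself fixes ANOVA with no imputation for any missing data, and here the value does not exist, so omission from the ANOVA follows from the stated rules.

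Fourth, the article gives no time data. The delay is assumed, and so is the simulation's base time. This stands, and the sizes are illustrations only.

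**Conclusion.** The concern holds as a badly fixed endpoint and should be corrected. On a listed primary endpoint, the recorded time of a multi-attempt patient depends on an unstated convention.

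- If only the successful pass is timed, the difference is understated by about 0.10 × D, or 3 to 9 s for an assumed D of 30 to 90 s. This rests on that reading, on the assumed D, and on pilot rates from 30 patients per arm. It is not an expected bias of the trial. The error would run toward no difference, so it would cost sensitivity and would not produce a false claim for TAS.
- If repeat glotticoscopies are counted inside and outside the negotiation clock, the error runs the other way, lengthening recorded time in the arm with more repeat attempts.
- Never-intubated patients have no value on any reading. Their loss from the ANOVA depends on outcome, runs against the intention-to-treat statement, and would favour the arm with more failures. At about 0 to 2 of 79 PIS patients, with 2 requiring 50% failure at both later attempts, it is a conflict of principle with little numerical weight. A reader might infer a wholesale breach of intention to treat, which the article does not support.

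**What to change.** Three changes of wording:

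1. Define total intubation time as one continuous clock, from first entry of the blade between the teeth on attempt 1 to the black line passing the cords on the successful attempt. State that withdrawal, reshaping and re-oxygenation are included.
2. State how patients not intubated within three attempts enter the time comparison: given the worst rank, or censored when stylet intubation is abandoned. Analyse with a rank-based or log-rank test stratified by the ADA stratum used for randomization, at least as a supporting analysis to the ANOVA.
3. Report the successful-pass time (glotticoscopy plus negotiation on that attempt) as a secondary endpoint.

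The cost is the wording and at most one more time stamp, with no change to clinical management. Eleven patients had been recruited at submission, so it must be checked whether their start and end times were recorded. The drawback is that continuous times will be more skewed, which strains the ANOVA, and less comparable with single-pass times in other studies. They also take in the gap between best view and handover of the tube, which the present sum leaves out even for a single pass. Keeping successful-pass time as secondary preserves the comparison with other studies.

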**Figure 1 F1:**
[figure not shown]
**Enhanced angulation of the D-blade of the C-Mac™ videolaryngoscope. (a)** Shown is the sharper blade angulation of the D-blade of the C-Mac™ videolaryngoscope versus the conventional Macintosh laryngoscope blade. **(b)** The natural curvature of the traditional endotracheal tube does not match the enhanced angulation of the D-blade of the C-Mac™ videolaryngoscope.

Despite several advantages offered by the videolaryngoscopes, their major handicap is their enhanced anterior angulation of the blades, such as that of the Glide-Scope™ (Verathon Medical, Bothell WA, USA), the McGrath series 5 (Aircraft Medical, Edinburgh, UK), and the TruView™ PCD devices (Truphatek International Limited, Netanya, Israel), which makes viewing of the laryngeal structure easier [1,2], but negotiation of the endotracheal tube (ETT) towards the glottis difficult, and at times a failure [7,8]. This is attributed to the fact that the tip of the ETT has to pass around the steep angle of the videolaryngoscope blade to site with the larynx. An un-styleted ETT is unable to do this as its inherent radius of curvature of nearly 14 cm [9] cannot align with the acute radius of curvature of the D-blade of the C-Mac™ or other videolaryngoscopes, which is 7 to 8 cm (Figure 1b). This may result in a longer intubation time [10]. It is recommended that a pre-shaped, styleted tube be used during endotracheal intubation with a videolaryngoscope to overcome this problem [11]. The Glide-Scope™ and TruView™ PCD have their own pre-shaped dedicated rigid stylets, which do not permit reshaping. Unfortunately, the pre-shaping of the ETT with a stylet may not always suit an individual patient’s need [12]. In such a patient, if the stylet permits, such as the malleable Portex™ intubation stylet (PIS) (Smiths Medical ASD, Inc. Norwell, MA, USA], the ETT-stylet assembly has to be taken out and re-shaped before making another attempt at tracheal intubation. This may delay endotracheal intubation with a potential increased hemodynamic response and soft-tissue trauma [13,14].

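### Blood pressure and pulse readings timed only from completed intubation may miss transient changes during failed passes, withdrawal and reshaping, the step the protocol names as a source of hemodynamic disturbance

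*Protocol article*

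**What the plan says.** The endpoint paragraph of the protocol article's Methods (after Figure 4) lists hemodynamic disturbance as a safety endpoint. The schedule is "blood pressure and pulse rate would be recorded before intubation, 1 minute and 5 minutes post-intubation", and the event rule is "≥20% change from the baseline value will be considered clinically important". Both later readings are counted from intubation. Nothing is scheduled during an attempt or between attempts. The same paragraph allows "a maximum of three attempts, after which an alternative technique will be used". Arrhythmia, cardiac arrest and trauma are listed without a time window.

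The rationale is given in two places. The Abstract says of withdrawing the assembly for reshaping: "This may cause soft tissue injury and hemodynamic disturbance". The Background says of the same step: "This may delay endotracheal intubation with a potential increased hemodynamic response and soft-tissue trauma". The Background then states the hypothesis that intubation over the articulating stylet "will also attenuate the hemodynamic response and reduce the possibility of soft-tissue trauma", compared with PIS-aided intubation.

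**The concern.** The only route to a hemodynamic difference that the document spells out is taking the assembly out, reshaping it and trying again, with the delay this causes. The schedule has no reading while that happens. A change that arises in a failed pass and settles before 1 minute after the final, successful pass leaves no trace in the data.

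The clock also depends on the course of the intubation. Readings start at completed intubation, so the time from first instrumentation to first reading grows with the duration of intubation. Duration and first-attempt success are primary endpoints that the trial expects to differ by arm.

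At stake is a safety comparison that carries a stated hypothesis. If short-lived peaks occur mainly in repeat attempts, and repeat attempts mainly in the PIS arm, the recorded contrast could be smaller than the true one.

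**Working it through.** **Inputs.** From Statistical considerations: pilot first-attempt success of 27/30 = 90% (PIS) and 30/30 = 100% (TAS), and a final sample of 158 with equal allocation, so 158/2 = 79 per arm. From Methods: an attempt is counted when the laryngoscope or tube has to come out for re-oxygenation or reshaping. Failure of the first attempt therefore generally implies a withdrawal.

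**The plan's own figure.** The calculated total of 154 can be approximated. With pooled variance, n per arm = (1.960 + 0.842)² × 2 × 0.95 × 0.05 / 0.10² = 74.6, so 75 per arm and 150 in total, within 3% of 154. The same formula with 99.9% in place of 100% gives 77 per arm, which is 154. The present point does not depend on this figure.

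**Patients with an unobserved repeat attempt.** Expected number = n × (1 − first-attempt success).
- PIS: 79 × 0.10 = 7.9 (95% binomial range 3 to 13 if the true rate is 10%).
- TAS: 79 × 0 = 0.
- With 77 per arm, PIS is 7.7.

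The pilot fixes these rates only loosely. The exact 95% interval for 3/30 is 2.1% to 26.5%, or about 2 to 21 of 79. For 0/30 the upper limit is 11.6%, or about 9 of 79.

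**Events that could be lost.** Let f be the fraction of an arm with a repeat attempt. Let m be the share of those patients who cross 20% in the gap and are back under 20% at both 1 and 5 minutes. The event rate lost in an arm is f × m.
- PIS at planning rates: 0.10 × m, so between 0 (m = 0) and 10 percentage points (m = 1).
- TAS at planning rates: 0 × m = 0.

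The document gives no time course, so m is unknown. Ten points is a ceiling, not an estimate.

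**Timing, with one anchor for both arms.** Let T be the time from first blade insertion to completed intubation. The first later reading falls at T + 1 minutes after insertion. As an assumed illustration, a PIS patient with a repeat attempt has T = 2 and is first read at 3 minutes. A first-pass TAS patient with T = t is read at t + 1. The difference is 3 − (t + 1) = 2 − t minutes. Counted from completed intubation, both are read at 1 minute. The delay since first instrumentation differs, but the delay since the last does not.

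**Why any added window must have equal length.** If each reading has chance p of crossing 20% through fluctuation alone, k independent readings give 1 − (1 − p)^k. An extreme value over a window that lengthens with attempts would raise k in multi-attempt patients and so create a difference by itself.

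**The case against.** A reader might infer that the response the trial hopes to reduce is not measured at all. The document does not support that. The hypothesis concerns TAS-aided against PIS-aided intubation as a whole and is not limited to failed passes. Baseline, 1-minute and 5-minute readings in both arms do address it. At the planning rates about 150 of 158 patients (158 − 7.9) succeed at the first attempt and have no failed pass to miss.

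A reader might also infer that the arms cannot be compared, or that the result must be pushed towards no difference. Neither follows. A uniform delay after the last stimulus is a coherent design, and the successful pass in a multi-attempt patient is itself a stimulus that ends 1 minute before the reading. If responses accumulate over attempts, the 1-minute value may show it.

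Three further objections have weight. Patients moved to an alternative technique need three failed attempts, and no rate is given for that. Attempts are counted, so the existing readings can be examined by number of attempts. The article condenses a fuller protocol, which might schedule more readings.

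These objections limit the point but do not remove it. The article states the schedule explicitly and gives no reading at the step that its own rationale names. Examining results by number of attempts cannot recover a value that was never recorded.

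**Conclusion.** The point holds as a modest mismatch between rationale and measurement. Transient changes in pressure or pulse during a failed pass, withdrawal or reshaping have no scheduled reading and may be missed. At the planning rates this concerns about 8 of 79 PIS patients and none of 79 TAS patients. The loss in the PIS event rate is therefore at most 10 percentage points, and any response that persists to 1 minute is still captured.

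The size rests on the pilot rates, which are imprecise, and on an unknown time course. Bias towards no difference is possible but not shown. Only the pressure and pulse safety comparison is affected; arrhythmia, cardiac arrest and trauma are not tied to the 1- and 5-minute times.

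**What to change.** Keep the 1- and 5-minute post-intubation readings as planned. Add, from the monitor already in use, one reading just before first blade insertion as baseline and one every minute after it, over a single window of fixed length that is the same for every patient in both arms. First blade insertion is already timed as the start of glotticoscopy time. The team should set the window length in advance, long enough for most repeat attempts to fall inside it; the document gives no intubation times from which to derive it.

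Compare the arms on the existing 20% rule and on the maximum change from baseline within that common window. Include all randomised patients, also those moved to an alternative technique. This fits the stated intention-to-treat analysis and gives those patients a defined measurement.

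The cost is a few more recorded values per patient and a case-report-form change. The primary endpoints and sample size stay as they are. Under Trial status, 11 patients had been recruited at submission, so a change made then would have covered nearly the whole trial. Patients already treated would have only the planned readings, unless monitor records were kept.
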